Phycocyanin (PC) is one of the main pigments of the algae *Spirulina*, which also contains proteins, β-carotene, assimilable iron, γ-linoleic acid, and vitamin B12, and is used as a dietary supplement. The chemical structure of PC is very close to the structure of bilirubin, a degradation product of hemoglobin. Bilirubin is known to be an important physiological antioxidant that combats reactive oxygen species.

In 1998, Cuban researchers described the antioxidant activity of PC [6] for the first time. These authors determined that PC was able to scavenge the hydroxyl radical (OH^-^), the alkoxyl radical (RO), and the superoxide anion (O_2_^−^). It was also able to inhibit lipid peroxidation [6]. In addition, they described the anti-inflammatory properties of PC for the first time [7].

In 2018, Renugadevi et al. revealed that the PC pigment could be a promising antioxidant compound and with further study, that it has the potential as an antioxidant agent to overcome oxidant-induced diseases [8].

Our hypothesis is to test Spirulina liquid extract that has been greatly enriched with PC (SLPC) in patients with gastrointestinal cancer and treated with platinum salts, to reduce or cancel out the neuropathy associated with this treatment, which is still an unresolved medical need. The SLPC contained in the food supplement SPIRULYSAT® (produced by AlgoSource) has already been tested for metabolic syndrome (NCT02817620). Studies of SPIRULYSAT® in the murine model of non-alcoholic steatohepatitis have shown very strong anti-oxidant activity [9]. The SLPC used in this protocol will be five times more concentrated but is still produced by the same laboratory (PHYCOCARE®).

In brief, firstly, it is generally accepted that no pharmacologic agent has been definitively shown to prevent platinum salt-induced neurotoxicity [10]. Secondly, although duloxetine, a non-selective serotonin reuptake inhibitor antidepressant with non-opioid pain-relieving properties, has been shown to be effective in ameliorating neuropathic pain, clinical experience has not, to date, validated the trial data [11]. Thirdly, as already mentioned, the dose of platinum salts can be reduced so as not to induce neuropathy, possibly leading to a drastic reduction in the therapeutic effects. Fourthly, spirulina and more precisely PC has anti-oxidant effects and in murine models, it protects the kidneys from the nephrotoxic effects of cisplatin [12].

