### Objectives {7}

The primary objective is to demonstrate a 50% decrease in neurotoxicity grades of 2 or above at cycle 9 (4 months after the start of oxaliplatin-based chemotherapy) in the SLPC arm.

The secondary objectives are to compare the following in both arms:➢ Percentage of patients who stopped oxaliplatin due to neurological toxicity➢ Percentage of patients with an oxaliplatin dose decrease➢ Neurological toxicities according to the Common Terminology Criteria for Adverse Events (CTCAE) v5.0➢ Overall toxicity (including hematological toxicity, gastrointestinal toxicity, etc.)➢ Patient’s quality of life according to the EORTC-QLQ-C30 questionnaire

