### Outcomes {12}

The primary endpoint is the rate of neurotoxicity according to US NCI (National Cancer Institute) criteria in both arms 4 months after the beginning of oxaliplatin-based regimen. NCI criteria are listed in Table 4.

**Table 4 Tab4:** US National Cancer Institute common toxicity criteria (NCI-CTC)

Oxaliplatine dosage adjustment according to neurotoxicity				
Neurotoxicities	Grade	Toxicity duration		
		1 to 7 days	> 7 days	Persistent between cycles^**a**^
Paresthesias/dysesthesias^b^ that do not interfere with fine motor skills	1	No dose reduction		
Paresthesias/dysesthesias^b^ that interfere with fine motor skills but do not affect activities of daily living (ADLs)	2	No dose reduction		75% of the dose
Paresthesias/dysesthesias^b^ with pain or decreased fine motor skills that affect activities of daily living (ADLs)	3	1st time: 75% of the dose 2nd time: 50% of the dose		Discontinue treatment
Persistent or incapacitating or lifethreatening paresthesia/dysesthesia	4	Discontinue treatment		
Acute toxicity: laryngeal-pharyngeal dysesthesia^b^ (during or within 2 h after infusion)	NA	Extend the oxaliplatin infusion to 6 h on the next treatment.	NA	

^a^Toxicity still present at the beginning of the next cycle

^b^May be caused by the cold

The secondary outcomes are:⇨ Time frame for definitive discontinuation or decrease in oxaliplatin treatment. The dose or discontinuation of oxaliplatin will be noted at each chemotherapy visit, in accordance with the process established in Table 3⇨ Dose intensity of oxaliplatin noted at each chemotherapy visit (see Table 3)⇨ Neurological adverse events at the following hospital visits: baseline, M4, and M9/termination visit⇨ Nerve electrodiagnostic examination (EDX) and neurology questionnaire: Overall Neuropathy Limitation Scale (ONLS) French translation according to Graham et Hugues [14] at baseline, M4 and M9/termination visit⇨ Adverse Events collected at each chemotherapy visit or in patient diary⇨ Quality of life questionnaire: QLQ C30 at baseline, M4 and M9/termination visit

Note that when a patient discontinues the study treatment early for whatever reason, an early termination visit will be conducted if the patient’s condition allows.

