### Sample size {14}

Simon’s two-stage design [15] will be used. The null hypothesis that the true response rate is 0.60, the proportion of neurotoxicity targeted, will be tested against a one-sided alternative. In the first stage, 31 patients will be accrued. If there are 18 patients or fewer with grade 1 neurotoxicity among these 31 patients in the SLPC arm, the study will be halted. Otherwise, 24 additional patients will be accrued, making a total of 55. The null hypothesis will be rejected if 38 or more responses are observed in 55 of the SLPC arm patients. With a type I error rate of 0.05 and a power of 0.90, 55 patients will be enrolled in each arm, that is to say, 110 patients.

All the previous hypotheses account for a lost-to-follow-up rate at 4 months of 20%.

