## Statistical methods

### Statistical methods for primary and secondary outcomes {20a}

Descriptive analyses will be conducted for all variables collected. Point estimates and 95% confidence intervals will be calculated for qualitative and quantitative variables. For estimates obtained using a small sample, the medians and interquartile intervals (for quantitative variables) and exact confidence interval (for qualitative variables) will be provided. All analyses will be performed with the use of R software (version 4.0) or SAS software (version 9.4).

To fulfill the main objective of this study, the prevalence of neurotoxicity of grade 2 or above in both arms will be estimated using linear mixed regression, taking into account the center effect (random effect). The second step will be to adjust this estimate based on known risk factors (gender, age, etc.).

For the secondary analyses:Comparison of time before cessation or reduction of chemotherapy treatment will be estimated using the Kaplan-Meier method and tested with the log-rank test;Comparison of patients with a decrease in treatment due to neurological toxicity will take place via mixed linear regression on both treatment arms;Progression of grades 3 and 4 neurological adverse events at baseline, M4, and M9 (or at the last visit if earlier) will be tested using mixed linear regression with a random center effect;EDX data will be compared using Fisher’s exact test and the Wilcoxon-Mann-Whitney test;The chi-square test or Fisher’s exact test will be used to compare Adverse Events in both arms;Progression of grades 3 and 4 neurological QLQ C30 at baseline, M4, and M9 (or at the last visit if earlier) will be tested via mixed linear regression with a random center effect; andMedian progression-free survival will be estimated and plotted using the Kaplan-Meier method and the response rate will be estimated as a percentage with a 95% confidence interval.

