### Interim analyses {21b}

A futility analysis will be performed according to Simon’s method [15]. Enrolment will continue during the futility analysis. The study will be halted if there are fewer than 18 responders (i.e., patients with grade 1 neurotoxicity) in the first 31 patients enrolled in the SLPC arm.

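### The two-stage rule counts only grade 1 patients as responders, so a patient kept free of neuropathy is scored as a failure

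*Protocol article*

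**What the plan says.** The protocol article describes the favourable or unfavourable outcome in several places.

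- **Objectives {7}:** the aim is to "demonstrate a 50% decrease in neurotoxicity grades of 2 or above at cycle 9".
- **Statistical methods {20a}:** for the main objective, "the prevalence of neurotoxicity of grade 2 or above in both arms will be estimated".
- **Outcomes {12}:** "The primary endpoint is the rate of neurotoxicity according to US NCI (National Cancer Institute) criteria in both arms", with no grade cut.
- **Sample size {14}, stage 1:** "If there are 18 patients or fewer with grade 1 neurotoxicity among these 31 patients in the SLPC arm, the study will be halted".
- **Sample size {14}, final rule:** "The null hypothesis will be rejected if 38 or more responses are observed in 55 of the SLPC arm patients". No grade is named here.
- **Interim analyses {21b}:** the trial stops with "fewer than 18 responders (i.e., patients with grade 1 neurotoxicity) in the first 31 patients enrolled in the SLPC arm". This is the only place where the document says what a responder is.

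The Background {6a} says the product is given "to reduce or cancel out the neuropathy associated with this treatment". Sequence generation {16a} stratifies on neuropathy stage 0 or 1, so grade 0 is a recognised state in this trial.

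**The concern.** The complement of grade 2 or above is grade 0 or 1. The decision rules count grade 1 alone, and no section adds grade 0 for them. The quantity compared with 18 of 31 and 38 of 55 is therefore not the complement of the quantity named in the objective and estimated in the main analysis.

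The error works against the product. A patient moved from grade 1 to grade 0 lowers the responder count by one and leaves the prevalence of grade 2 or above unchanged. A patient moved from grade 2 to grade 0 improves that prevalence but adds nothing to the count. The trial could be stopped for futility, or declared negative, while the prevalence reported under {20a} shows the target met.

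**Working it through.** **Inputs from the document.** Stage 1 has 31 patients in the SLPC arm, with a halt at 18 or fewer ({14}) or at fewer than 18 ({21b}). The final rule is success at 38 or more of 55, so stage 2 adds 24 patients. The null response rate is 0.60, with a one-sided type I error of 0.05 and power of 0.90.

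**Assumptions.** The alternative rate is not printed. If 0.60 is the null share below grade 2, then 40% are at grade 2 or above. The 50% decrease in {7} takes that to 20%, so 80% are below grade 2. The grade 0 share at cycle 9 is not given either, so a range is shown.

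**Formulas.** Let p be the probability that a patient is counted as a responder, X1 ~ Bin(31, p) and X2 ~ Bin(24, p).

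- P(halt) = P(X1 ≤ 18), or P(X1 ≤ 17) under the {21b} boundary.
- P(success) = Σ over x = 19 to 31 of P(X1 = x) × P(X2 ≥ 38 − x).

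**The plan's own figures.** At p = 0.60 the printed rule has an exact type I error of 0.104, not 0.05. Its power is 0.872 at p = 0.75 and 0.980 at p = 0.80. The stated pair of 0.05 and 0.90 is therefore not reproduced. That is a separate defect, and the present point does not depend on it.

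**Intended definition (grade 0 or 1).** With p = 0.80, P(halt) = 0.0044 and P(success) = 0.9802.

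**Printed definition (grade 1 only).** For the same product, p = 0.80 − grade 0 share:

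| Grade 0 share | p (grade 1 share) | Expected count, 31p | P(halt, ≤18) | P(halt, <18) | P(success, ≥38/55) |
|---|---|---|---|---|---|
| 0% | 0.80 | 24.8 | 0.0044 | 0.0013 | 0.9802 |
| 10% | 0.70 | 21.7 | 0.1069 | 0.0534 | 0.6150 |
| 20% | 0.60 | 18.6 | 0.4805 | 0.3399 | 0.1042 |
| 30% | 0.50 | 15.5 | 0.8595 | 0.7634 | 0.0031 |
| 40% | 0.40 | 12.4 | 0.9865 | 0.9680 | 0.0000 |

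The success column uses the {14} boundary. With the {21b} boundary its first four entries are 0.9816, 0.6210, 0.1061 and 0.0032.

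Every row has the same true prevalence of grade 2 or above, 20%. Only the split between grade 0 and grade 1 changes. At a 20% grade 0 share, a product that meets its target has the same operating characteristics as the null.

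The results depend only on the grade 1 share. If 70% rather than 80% were below grade 2, each probability would be reached at a grade 0 share ten percentage points lower.

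**Limiting case, which needs no assumption.** If every patient stays at grade 0, the count is 0 of 31 and the trial is halted with certainty.

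**The case against.** **Grade 1 or less was surely meant.** This is likely, since the objective and the main analysis agree on the cut. It makes the point a wording error rather than a deliberate choice. The full protocol (version 2) is not shown and may word the rule correctly. But the article does not leave the definition open. It fixes one explicitly, and the stage 1 rule repeats it in another section. The document also says that no data monitoring committee was set up, so that safeguard at the interim count is absent. Changing the definition once the stage 1 data are known would be open to challenge.

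**The final rule names no grade.** This is true, and applying grade 1 to the 38 of 55 is an inference. It is a strong one: in a two-stage design the stage 1 responses are carried into the final count, and the document offers no other definition. The halting probabilities do not rely on this inference; the success probabilities do.

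**Grade 0 may be rare.** The Discussion says that some degree of neuropathy occurs in nearly all patients, and with no grade 0 patients the printed rule behaves as intended. This limits the size of the harm. The statement describes oxaliplatin-treated patients in general, whereas an effective product would raise the share. The stage 0 stratum describes baseline only and says nothing about the share at cycle 9. The 20% row and those below it are illustrations, not forecasts.

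**The endpoint wording in {12} is loose rather than contradictory.** Agreed. It is worth tidying in the same edit but carries little weight alone.

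**Conclusion.** The concern holds. Applied as written, the rule scores complete protection as failure, and its count is not the complement of the primary outcome. The direction of the error needs no assumption.

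The size is conditional on two figures that the document does not give: the 80% below grade 2 and the grade 0 share. Under the first, a 10% grade 0 share already cuts the chance of success from 0.98 to 0.62 and raises the chance of a futility halt from 0.004 to 0.11. At 20% the figures are 0.10 and 0.48. Because this definition governs both the futility stop and the only success criterion printed, it must be corrected.

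**What to change.** - In {14} and {21b}, define a responder as a patient with neurotoxicity of grade 0 or 1, that is, none of grade 2 or above, at day 1 of cycle 9. State that the same definition applies to the stage 1 count and to the final count of 55.
- In {12}, state the primary endpoint as the proportion of patients with grade 2 or above at that visit. The responder count, the endpoint and the prevalence in {20a} are then exact complements.
- In the same edit, say which quantity 0.60 refers to. The current sentence gives it two labels: "The null hypothesis that the true response rate is 0.60, the proportion of neurotoxicity targeted, will be tested against a one-sided alternative".

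The cost is wording in three sections, with no extra data or patients, provided it is done before the first look.

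The new wording alone does not make the rule valid. The two stage 1 boundaries (18 or fewer against fewer than 18) and the exact type I error of 0.104 are separate defects that still need to be resolved.

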### Methods for additional analyses (e.g., subgroup analyses) {20b}

No additional analyses are planned.

### Methods in analysis to handle protocol non-adherence and any statistical methods to handle missing data {20c}

If missing, unused, or invalid data are highlighted, two methods will be used. With regard to the prevalence rates detailed in the objectives, estimates will be created based on the modified intention-to-treat population. For the primary objective only, multiple imputation techniques will be applied to all the covariates and to neurotoxicity grade for sensitivity analyses.

### Plans to give access to the full protocol, participant-level data and statistical code {31c}

The datasets analyzed in the present study and the statistical code are available from the corresponding author on reasonable request, as is the full protocol.

## Oversight and monitoring

### Composition of the coordinating center and the trial steering committee {5d}

The Scientific Committee was created and coordinated by Prof. [name] and Dr [name]. Its membership comprises Prof [name], neurologist, a biostatistician and methodologist, the study coordinator, and the project manager of the clinical investigation center (CIC 1413). The Steering Committee is composed of the members of the Scientific Committee with the addition of the data management team, the study nurse who coordinates assistance for patient enrolment in the other centers, and the monitoring Clinical Research Assistant. The sponsor’s project manager coordinates this committee and drafts the “Property newsletter” which will include, among other things, the latest news on patient enrolments and amendments to the protocol.

### Composition of Data Monitoring Committee, its role and reporting structure {21a}

SLPC is contained in PHYCOCARE®, a dietary supplement, leading to a low-risk intervention in this study; a Data and Safety Monitoring Committee was thus irrelevant.

### Adverse event reporting and harms {22}

All subjects will be followed up for adverse event collection, through self-reporting in the patient’s diary and monthly, at the time of the visit, based on clinical and biological examination. Neurological toxicity will also be monitored by EDX. In addition, between visits, as well as all subjects receiving chemotherapy, patients are asked to contact the clinical team in case of difficulties or toxicity.

The expected ARs are associated with:▪ PHYCOCARE®Spirulina has been the subject of preclinical and clinical studies. Preclinical data have not shown toxicity of spirulina at high doses (for administered doses up to 30g/kg/day or ad libitum in mice). In the numerous clinical studies carried out at doses of up to 19g/day of dry spirulina, only a few gastrointestinal (moderate vomiting and diarrhea episode) and headache-type adverse effects linked to the consumption of spirulina have been reported.Products containing spirulina may be contaminated with cyanotoxins, with bacteria or by metallic trace elements (Report of the French Agency for Food, Environmental and Occupational Health Safety (ANSES) available from: https://www.anses.fr/fr/system/files/NUT2014SA0096.pdf); no clinical impact (infection/signs of poisoning) is expected, however.▪ The placebo:° Hypersensitivity reaction to colorant (dry blue) or *Cinnamomum camphora cineol* may be expected° Toxicity: camphor laurel is mildly toxic to humans, and mild symptoms may occur if large quantities are eaten. All parts of the plant are poisonous and can cause nausea, vomiting, and respiratory distress. Allergic skin reactions can also occur° Headache (moderate and intermittent),° Constipation or loose stools° Elevated transaminasesThe protocol:° Disagreement or anxiety about randomization to the placebo arm° EDX: mild discomfort related to electrical stimulation and muscle needle examination° Asthenia, boredom, due to difficulty or inability to complete the questionnaires,The disease:° Anxiety/depression (including sleep disorders, suicide attempts)° Progression of the disease° Metastasis and related symptomsChemotherapy and associated treatments. The main adverse reactions due to chemotherapy are:° Hematological toxicity° Gastrointestinal toxicity (nausea, vomiting, diarrhea, stomatitis)° Cutaneous-mucosal toxicity° Neurological toxicity° FatigueChemotherapy also requires standard prophylaxis for drug toxicity and the risk of thrombosis, and pain killers.

All these drugs are used in their marketing authorization indications, so the expected adverse drug reactions are as listed in each Summary of Product Characteristics.

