### Intervention description {11a}

Being double blind, the study treatment, the comparator and its corresponding placebo will be managed by the sponsor and AlgoSource. The patient must begin the study treatment 3 days before the chemotherapy regimen. This regimen is counted in cycles that last around 14 days and begin on Day1 (D1) of each chemotherapy cycle. No study treatment must be taken on chemotherapy treatment days.

The SPLC/placebo prescription will cover 1 month of treatment. Participants will be given a patient diary for the entirety of the study. From D3 to D1 before the first chemotherapy cycle: patients will take SPLC or placebo (one ampoule per day, neat or diluted in a glass of water). If vomiting occurs immediately after taking the SLPC dose, the patient should retake the SLPC dose. On chemotherapy days (D1 to D3), the patient does not take SLPC/placebo. From D4 to D14 SLPC/placebo must be taken once a day and 1 h before or 2 h after food and taking the antiemetic. The same schedule will be used during induction chemotherapy for 12 cycles, as shown in Fig. 2A.

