**Fig. 2 Fig2:**
[figure not shown]
Schedule of trial treatment in chemotherapy cycles

After induction chemotherapy, the patients on maintenance therapy or targeted therapy will continue to take spirulina for six cycles (3 months) after the last cycle of oxaliplatin (Fig. 2B). The same schedule will be applied for the patients who are not on maintenance chemotherapy (Fig. 2C). The complete trial schedule is shown in Table 2.

**Table 2 Tab2:** Study schedule

Assessments	Inclusion visit D-30 to D-4	Cycle 1	Cycle 1 to 12		Cycle 13 to 18	End of study visit / 28 days after last day of PHYCOCARE® /PLACEBO
		D-3 to D-1	D1 to D3	D4 to D14	D1 to D14	
Informed consent	X					
Medical History	X					
Clinical examination (Performance status (ECOG), vital signs, symptoms)	X		X (D1)		every 28 days	X
ONLS questionnaire	X		at M4 (C9D1)			X
QLQ-C30 questionnaire	X		at M4 (C9D1)			X
EDX	X		at M4 (C9D1)			X
Randomisation	X					
Scanner	at D-42					
PHYCOCARE® or placebo treatment		X		X	X (days without chemotherapy)	
Oxaliplatin-based chemotherapy			X			
Chemotherapy maintenance regimen					If applicable	
Adverse events (AE)		AE assessed at each patient visit				X
Treatment adherence (patient diary)		Compliance assessed at each patient visit				X

Note that the oxaliplatin dose is 85 mg/m^2^ and the dose adjustment is shown in Table 3.

**Table 3 Tab3:** Oxaliplatin dose adjustement

Scale	NCI-CTC grading for neuropathy
Grade 1	Asymptomatic, loss of deep tendon, reflexes, or paresthesia (including tingling), but not interfering with function
Grade 2	Sensory alteration or paresthesia (including tingling) interfering with function, but not ADL
Grade 3	Sensory alteration or paresthesia interfering with ADL
Grade 4	Disabling

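### Adverse-event collection is stated as both monthly and at every chemotherapy visit, and the follow-up window may depend on oxaliplatin duration, which the stated between-arm test ignores (modest effect)

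*Protocol article*

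**What the plan says.** The protocol article describes AE collection in three places.

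- Adverse event reporting and harms {22}: self-report in the diary and "monthly, at the time of the visit, based on clinical and biological examination". Patients are also asked to contact the team between visits if they have problems.
- Outcomes {12}: "Adverse Events collected at each chemotherapy visit or in patient diary".
- Table 2: "AE assessed at each patient visit". The clinical examination row has a visit on D1 in the cycle 1 to 12 column, then one every 28 days in cycles 13 to 18.

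On cycle length, Intervention description {11a} says: "This regimen is counted in cycles that last around 14 days".

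The end of AE follow-up is set by the product. The AE row of Table 2 is marked at the visit headed "End of study visit / 28 days after last day of PHYCOCARE® /PLACEBO". Outcomes {12} adds that "when a patient discontinues the study treatment early for whatever reason, an early termination visit will be conducted if the patient’s condition allows".

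Product duration is stated in two ways. The text before Table 2 says that patients on maintenance or targeted therapy "will continue to take spirulina for six cycles (3 months) after the last cycle of oxaliplatin", and gives the same schedule for patients without maintenance chemotherapy. Participant timeline {13} gives a treatment period of 9 months (18 cycles) for participants in general.

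For the analysis, Statistical methods {20a} says that the chi-square test or Fisher's "exact test will be used to compare Adverse Events in both arms". It gives no observation window.

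**The concern.** There are two linked problems.

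The first is a contradiction in data collection. A site following the harms section would question patients about AEs half as often during induction as a site following Outcomes or Table 2. Overall toxicity is a secondary objective, and the article states that there is no data and safety monitoring committee, so routine collection is the main source of safety information. Events missed through sparser questioning cannot be recovered later.

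The second is the observation window. If the product, and with it the last AE visit, is tied to the last oxaliplatin cycle, a patient who stops oxaliplatin early is observed for less time. Keeping patients on oxaliplatin is the benefit the trial hopes for, and stopping or reducing it is a secondary outcome. An effective product could therefore lengthen observation in its own arm. A simple comparison of the proportions with an event would then count some of the extra time as extra toxicity.

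**Working it through.** The plan gives no figure on this point to reproduce. What can be checked is the visit arithmetic, the length of the window, and the size of any distortion under stated assumptions.

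**Step 1: collection visits during induction.** Inputs: 12 cycles of about 14 days ({11a} and Table 2).
- Duration: 12 × 14 = 168 days.
- At each chemotherapy visit: 12 visits.
- Monthly: 168 / 28 = 6 visits (168 / 30.4 = 5.5 with calendar months).

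The two rules differ about two-fold. In cycles 13 to 18 (6 × 14 = 84 days), Table 2 gives 84 / 28 = 3 visits, so the monthly wording fits only that later phase.

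**Step 2: length of the AE window.** Counted from C1D1, with *k* oxaliplatin cycles, under the reading that the product ends six cycles after the last oxaliplatin:

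window = (*k* + 6) × 14 + 28 days

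| Oxaliplatin cycles | Window (days) | Share of full window |
|---|---|---|
| 12 | 280 | 1.00 |
| 8 | 224 | 0.80 |
| 6 | 196 | 0.70 |
| 4 | 168 | 0.60 |

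Under the fixed 18-cycle reading of {13}, the planned window is 18 × 14 + 28 = 280 days for everyone, and this source of difference disappears.

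**Step 3: distortion of a crude proportion.** Assumptions, none of them in the documents:
- the hazard of a given AE is constant and equal in both arms;
- 40% of patients have the AE by day 280;
- 40% of placebo and 20% of SLPC patients stop oxaliplatin after cycle 6, and the rest complete 12 cycles.

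Risk at 196 days = 1 − 0.60^0.70 = 0.301. The loss compared with 280 days is 0.400 − 0.301 = 0.099. The spurious excess on SLPC is (0.40 − 0.20) × 0.099 = 0.020, or about 2 points.

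Range, keeping the 20-point difference in stopping:
- Low: stop after cycle 8, 20% risk at day 280. 0.20 × [0.20 − (1 − 0.80^0.80)] = 0.20 × 0.036 = 0.007.
- High: stop after cycle 4, 60% risk. 0.20 × [0.60 − (1 − 0.40^0.60)] = 0.20 × 0.177 = 0.035.

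**Step 4: comparison with sampling error.** With 55 per arm and a 40% risk, the standard error of the difference is √(2 × 0.4 × 0.6 / 55) = 0.093, or 9.3 points (the same at 60%). By normal approximation, a 2-point shift moves the two-sided 5% rejection rate to about 5.5%, and a 3.5-point shift moves it to about 6.6%.

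**Step 5: is a common period available?** C9D1 falls 8 × 14 = 112 days after C1D1. Even with oxaliplatin stopped after one cycle, the step 2 formula gives (1 + 6) × 14 + 28 = 126 days. Everyone who stays on the product as scheduled is therefore still under AE follow-up at C9D1, whichever reading of duration applies. Only patients who discontinue the product itself may leave earlier.

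**The case against.** The case on the other side is substantial.

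- **Table 2 can be taken as the operating rule, and both arms follow it.** True: the discrepancy in visit frequency is not a source of bias between blinded arms. It is still a contradiction that sites could resolve differently.
- **The oxaliplatin-dependent window is only one reading.** Participant timeline {13} states 18 cycles, and the six-cycle sentence opens by referring to the period after induction. This stands. The text does not say what happens to product duration when oxaliplatin is dropped early, so the window problem is conditional on how the two statements are reconciled.
- **Exposure adjustment belongs in the analysis plan.** Its absence from a condensed article is indeed no defect. What remains is that the article does name a test, and that test takes no account of observation time. Trial design {8} also calls the trial non-comparative and not powered to compare arms. That lowers the stakes but does not withdraw the test.

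Some stronger readings are tempting but not supported.

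- A reader might infer that AE collection ends with the product. Table 2 schedules it 28 days after the last dose.
- A reader might infer that the change from 14-day to 28-day visits biases the comparison. It applies to both arms, and the diary and between-visit contact remain in place.
- A reader might infer that the SLPC arm must show more patients with any AE. That requires oxaliplatin duration to differ by arm. The Discussion also says nearly all patients have some degree of neuropathy, so an any-AE proportion would be close to its ceiling in both arms.
- Larger distortions can be calculated. Ten months of follow-up against eight, at monthly hazards of 0.05 to 0.20, gives gaps of 6 to 8 points. That requires every patient in one arm to be followed two months less, whereas the step 3 scenario gives a mean difference of 0.20 × (280 − 196) = 17 days.

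**Conclusion.** The point holds in limited form. The conflict between the harms section and Outcomes with Table 2 is plain on the page and amounts to a two-fold difference in visit-based AE collection during induction. The two statements on product duration also need reconciling, because they decide whether AE follow-up is the same planned length for all patients or depends on when oxaliplatin stopped.

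If it depends on oxaliplatin, the crude between-arm comparison can be distorted, but only modestly: about 2 points, from 0.7 to 3.5, against a standard error of about 9 points. These figures rest on the assumed stopping rates, an equal constant hazard and the literal six-cycle reading. The documents give none of the rates, so the actual size cannot be known from them. The reason to act is that the remedy is cheap and a collection rule cannot be repaired after the data are in.

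**What to change.** 1. In Adverse event reporting and harms {22}, replace the monthly wording so that it agrees with Outcomes {12} and Table 2: AEs recorded at every scheduled visit, which means D1 of each of cycles 1 to 12 and every 28 days in cycles 13 to 18, plus the end-of-study or early termination visit.
2. Reconcile the six-cycle sentence before Table 2 with the 18-cycle statement in Participant timeline {13}, and state the resulting end of AE follow-up for a patient who stops oxaliplatin early. Which duration applies is for the sponsor to decide.
3. In Statistical methods {20a}, keep the crude comparison and report beside it AE rates per patient-month by arm. Add a supportive comparison restricted to the period up to C9D1 (or day 113 counted from C1D1), using only visits already scheduled.

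The cost is wording in three sections and one extra safety table. No visits need to be added. The restricted comparison leaves later events to the rate table, and patients who discontinue the product before C9D1 will still have incomplete observation within it, which a footnote should say.
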